### Sample size

Sample size calculations for the cluster design applied a mean −1.3 height-for-age (HAZ) for the coast region (20) and a hypothesized 0.20 effect size (21). Thus, we estimate requiring a total sample size of 400 households, which includes ~4 clusters per arm (four villages per BMU) and 50–75 households per cluster – assuming 20% losses-to-follow-up (α = 0.05 and 1-β = 0.80). Although this is small number of clusters, we will apply matching techniques a priori and during data analyses (e.g., propensity score matching) to better ensure internal validity.

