## Methods and analysis

### Design

We aim to test the effectiveness of the multi-component *Samaki Salama* intervention as it intersects with nutrition security and fisheries sustainability in Kilifi County, Kenya. Table 1 details the specific aims and hypotheses.

**Table 1 T1:** Study aims and hypotheses.

**Study aims**	**Hypotheses**
1. Determine the effects of a multi-component social marketing campaign to promote fish nutrition, dietary diversity, and food safety on child growth	**Primary** Hypothesis 1: Children in combined intervention groups have increased height-for-age *Z* by 0.2 compared to children in the control Hypothesis 2: Children in combined intervention groups have increased weight-for-age *Z* by 0.10 compared to children in the control Hypothesis 3: Children in combined intervention groups have increased fish food intakes by 100 g compared to children in the control
	**Secondary** Hypothesis 4: Children in combined intervention groups have increased dietary diversity by 1.2 compared to children in the control Hypothesis 5: Children in combined intervention groups have reduced diarrheal morbidity by 5 percentage points compared to children in the control
	**Exploratory** Hypothesis 6: Children in the social marketing + traps intervention group have increased dietary diversity and fish intake compared to children in the social marketing only group
2. Measure the impact of modified fishing traps with escape gaps on catch dynamics and earnings	**Primary** Hypothesis 7: Fishers in the social marketing + traps intervention group have significantly increased fisheries yields of mature fish compared to fishers in the control
	**Secondary** Hypothesis 8: Fishers in the social marketing + traps intervention group will have significantly increased earnings compared to fishers in the control

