### Setting

The study will be carried out in five distinct areas in Kilifi County, Kenya: Mayungu, Uyombo, Takaungu, Kuruwitu, and Kanamai (Figure 3). Study sites were chosen based on established relationships with the research team, receptivity to the proposed intervention, and proximity and access to marine resources. Kilifi County covers an area of 12,370 km^2^ with a population of 1.45 million and average household size of 4.8 persons (22, 23). The population primarily relies on small-scale fishing, farming activities (raising livestock, tree-cropping, and food-crop production), tourism, and migration to urban centers for their livelihoods (22). Close to half the population lives in poverty (46.4%) and the stunting prevalence (39%) is nearly double the national average, indicating high levels of malnutrition (20, 24). Education levels are low, and the populations are marginalized with limited formal rights to the marine resources on which many of their livelihoods depend.

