### Analysis

#### Primary and secondary outcomes

Generalized linear regression modeling (GLM), allowing for non-normal distributions, will test the continuous outcomes of HAZ, WAZ, child dietary fish intake, child dietary diversity score, fisheries yield, and fish earnings. As a difference-in-difference analyses, change variables for each outcome will be examined (difference between baseline and endline). For the binomial outcomes of diarrhea morbidity (and other outcomes of stunting and underweight), we will estimate prevalence ratios by the GLM modeling with robust Poisson. If stunting prevalence in this population exceeds the acceptable threshold for use of odds ratios (0.2105), prevalence ratios (PRs) will be used to examine the intervention effect and were considered analogous to relative risk in this longitudinal study. The robust Poisson, with a classic sandwich estimator to correct the inflated variance of standard Poisson, is less affected by outliers.

To test for intervention effectiveness, the two intervention groups will be combined for all hypotheses except the secondary outcome of increased fisher earnings and exploratory hypothesis for differences between social marketing and social marketing + traps intervention groups. Regression models will be adjusted for potential confounding factors including age, sex of the child, corresponding baseline measures, and others found to differ significantly between the trial groups (e.g., maternal education). For fisheries yield, confounding factors will be used to adjust regression models, such as: water temperature, fishing ground area, coral cover, and seasonality. The *P* significance value for Type I error (and one-tailed test) will be *P* < 0.05 and corresponding 95% confidence interval. Diagnostics for regression model assumptions, structure and observations will be applied, and corrective procedures applied as necessary. If selection bias is widely detected with important differences across intervention and control communities, we will apply propensity score analyses (36). Data analyses will be performed with Stata software (version 16.0; StataCorp, College Station, TX) and R (4.1.2).

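### The sample-size statement does not fit the three-arm 200/100/100 design, and its 80% power cannot be reproduced from the printed inputs

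*Protocol article*

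**What the plan says.** The Sample size section takes a mean HAZ of −1.3 and "a hypothesized 0.20 effect size", and concludes with "requiring a total sample size of 400 households, which includes ~4 clusters per arm (four villages per BMU"). It adds "50–75 households per cluster – assuming 20% losses-to-follow-up", with "α = 0.05 and 1-β = 0.80". No SD, baseline–endline correlation, ICC or sidedness appears there.

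The Design section, the eligibility section and Table 2 fix three arms: 200 control, 100 social marketing, 100 social marketing plus traps. The Design section explains that two equal groups were planned at first and that the intervention group was later split.

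In Table 1, Hypothesis 1 targets 0.2 in HAZ. A second primary growth hypothesis ("Hypothesis 2: Children in combined intervention groups have increased weight-for-age" Z) targets 0.10. Both compare the pooled intervention groups with control.

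The Analysis section works with baseline-to-endline change, adjusts for baseline, and says that the "significance value for Type I error (and one-tailed test) will be" P < 0.05, alongside a 95% confidence interval. The Setting section states: "The study will be carried out in five distinct areas in Kilifi County, Kenya".

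**The concern.** Two things look wrong. First, the cluster count, the cluster size and the total do not agree with the arms as now defined. In a cluster design, the number and size of clusters largely determine precision, and here a reader cannot establish either for any arm.

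Second, 400 households is small for an effect of 0.20 at 80% power unless the analysed outcome varies little and clusters are nearly homogeneous with one another. The article prints neither quantity. If they are less favourable than the 80% requires, a null growth result would be read against a power that the study did not have. The point is sharper for WAZ, a primary hypothesis at half the HAZ effect on the same households.

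**Working it through.** **Cluster arithmetic (printed figures only)**

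- Three arms: 3×4×50 = 600; 3×4×75 = 900.
- Two groups: 2×4×50 = 400; 2×4×75 = 600.
- A 100-household arm: 100/4 = 25 per cluster over four clusters, or 100/75 = 1.3 to 100/50 = 2 clusters of the stated size.
- The 200-household control arm fits at the lower end: 4×50 = 200.

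So 400 is reproduced only by the two-group layout at 50 per cluster. The choice affects precision. With 20% loss, 50 per cluster leaves 40 analysed and 25 leaves 20. At an assumed ICC of 0.02, the design effect is 1 + 39×0.02 = 1.78 in the first case and 1 + 19×0.02 = 1.38 in the second.

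**What 80% power requires**

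Inputs: 400×0.8 = 320 analysed, 160 per side with the intervention groups pooled; difference 0.20; α = 0.05. The mean of −1.3 does not enter a comparison of two means.

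Largest SD×√DEFF = 0.20 / [(z_α + z_0.80)·√(2/160)], where √(2/160) = 0.1118.

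- Two-sided: 0.20 / [(1.960 + 0.842)×0.1118] = 0.64.
- One-sided: 0.20 / [(1.645 + 0.842)×0.1118] = 0.72.

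**Reading 0.20 as a standardised effect (SD 1, no clustering)**

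0.20/0.1118 = 1.789. Power is Φ(1.789 − 1.960) = 43% two-sided and Φ(1.789 − 1.645) = 56% one-sided. Reaching 80% takes 393 per side two-sided (786 analysed, 983 enrolled after dividing by 0.8) or 310 per side one-sided (620 analysed, 775 enrolled).

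**Reading 0.20 as HAZ units on a change score**

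The SD and ICC below are assumptions. DEFF = 1 + 39·ICC (40 analysed per cluster), four clusters per comparison group. Power is two-sided / one-sided.

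| SD | ICC | Normal approximation | t on 6 df |
|---|---|---|---|
| 0.6 | 0 | 84.6% / 90.9% | 70.1% / 83.6% |
| 0.6 | 0.01 | 71.5% / 81.2% | 56.3% / 72.1% |
| 0.7 | 0 | 72.4% / 81.9% | 57.2% / 72.9% |
| 0.7 | 0.02 | 48.2% / 60.7% | 36.4% / 52.0% |
| 1.0 | 0.05 | 17.9% / 27.3% | 14.1% / 23.6% |

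The largest SD that keeps 80% (normal approximation) is 0.64 / 0.72 at ICC 0, 0.54 / 0.61 at ICC 0.01, 0.48 / 0.54 at ICC 0.02 and 0.37 / 0.42 at ICC 0.05.

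If the cross-sectional SD is 1 (assumed), the change SD is √(2(1 − r)). Without clustering, SD 0.64 / 0.72 then needs a baseline–endline correlation r of at least about 0.80 / 0.74.

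**WAZ 0.10, granting 80% for HAZ 0.20**

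With the same SD and design effect, half the difference halves the standardised distance:

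- Two-sided: 2.802/2 = 1.401; Φ(1.401 − 1.960) = 29%.
- One-sided: 2.487/2 = 1.243; Φ(1.243 − 1.645) = 34%.

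**The case against.** The strongest reply is that the 80% has not been refuted. The SD and ICC may stand in the full protocol, and an article may leave them there. The analysed variable is a baseline-adjusted change, so an SD of 1 may be the wrong yardstick: with a cross-sectional SD of 1 and a correlation of 0.8 (both assumed), the change SD is 0.63 and the baseline-adjusted residual SD is 0.60. The only sidedness stated is one-tailed, and SD 0.6 with ICC 0.01 then gives 81%. This stands. A reader might infer that the study is certainly underpowered; the documents leave that undetermined.

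A reader might also infer that the cluster figures can never give 400. They can, at 2×4×50, and HAZ is indeed compared between two pooled groups. But the text says per arm, the study has three arms, and the upper end of the same range gives 600.

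The remark about four villages per BMU invites the inference of one BMU per arm, so that arm and BMU could not be separated. The documents do not support this: the parenthesis is ambiguous, and the Setting section does not map its five areas to BMUs or arms.

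Finally, the power calculation is stated for HAZ and claims nothing for WAZ. That is so, but WAZ is listed as primary, and the HAZ figure should not be taken to cover it.

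**Conclusion.** The cluster statement is wrong as written for the 200/100/100 design. It implies 600–900 households, and no 100-household arm can contain four clusters of 50–75. This conclusion needs no outside assumption.

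The 80% power is not reproducible from what is printed. It fails if 0.20 is standardised (43% / 56% before clustering). If 0.20 is in HAZ units, it holds only where SD×√DEFF is at most 0.64 / 0.72, which means a small SD and almost no clustering. The power values in the table rest on assumed SD and ICC, four clusters per comparison group and 40 analysed per cluster; a t reference on 6 df lowers all of them. WAZ 0.10 has about 29% / 34% even when HAZ is granted its 80%, provided that the SD and design effect are the same.

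It does not follow that a null growth result must be declared inconclusive in advance. That will depend on the confidence interval obtained.

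**What to change.** Keep 400 households and revise the Sample size section as follows.

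1. For each of the 200, 100 and 100 arms, give the number of clusters and the households per cluster, and reconcile these with the BMUs, the villages and the five study areas.
2. State whether 0.20 is in HAZ units or standardised, and give the SD of the analysed change (or the residual SD after baseline adjustment), the ICC and the sidedness, consistent with the Analysis section.
3. Recompute the power or the detectable difference for HAZ 0.20 and for WAZ 0.10 on that layout, allowing for the small number of clusters.
4. Replace the 80% figure if it does not reproduce.

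The cost is a recalculation and some rewording. No extra enrolment is needed, though the stated power may become less favourable.

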##### Fisher revenue

During fisheries yield data collection, enumerators will also ask fishers about their operational costs and the revenue generated from selling the fish. Fisher revenue will be represented as Kenyan shillings (Ksh) per fishing trip. These questions will be informed by cultural norms and objects such as food and equipment used as currency when Kenyan shillings cannot be estimated (e.g., bags of rice). Comparisons will be made at the landing site or BMU level to measure the change in earnings pre- and post-intervention as described by Wamukota et al. (35).

A range of other variables will be assessed to control for cofounding factors associated with the cluster design. These variables include but are not limited to child illness (a standard 2-week recall on infectious illnesses including cough, rhinorrhea, fever, and rash), household consumption and assets, and household decision making [Likert scale instrument that captures common domains of decision-making including purchasing decisions; decisions regarding service use (health, education); decisions regarding children's diet, health and education].

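### The stated clusters per arm cannot be squared with the five study areas, and on any reading few areas carry the treatment, so household-level tests are anti-conservative

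*Protocol article*

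**What the plan says.** The Sample size section says "we estimate requiring a total sample size of 400 households", based on "a hypothesized 0.20 effect size" in height-for-age Z (HAZ), "assuming 20% losses-to-follow-up", α = 0.05 and 80% power. It describes the structure as one "which includes ~4 clusters per arm (four villages per BMU") with "50–75 households per cluster". It concedes that this is a small number of clusters and answers with matching and propensity scores.

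The Setting section says: "The study will be carried out in five distinct areas in Kilifi County, Kenya". The Design section gives three groups of 200, 100 and 100 households. It explains that an original plan for two equal groups was changed because trap fishers and funds were too few. Communities associated with BMUs are matched and assigned without randomisation.

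The Analysis section describes a generalized linear model of change scores, one-tailed at 5%. It lists adjustment covariates but names no village, BMU or area term. It pools the two intervention groups for all hypotheses except fisher earnings and the exploratory comparison. For earnings, the Fisher revenue section says: "Comparisons will be made at the landing site or BMU level to measure the change in earnings pre- and post-intervention". For fisheries yield, the listed confounders are "such as: water temperature, fishing ground area, coral cover, and seasonality".

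**The concern.** The unit that receives the treatment also determines what else can change for a household over the year: local catch, prices, closures, livelihood shocks. Fisher workshops are held at BMU offices, traps are handed out at landing sites and BMU offices, and BMU orientations are part of the campaign. Spill-over is the stated reason for not randomising, which also argues against mixing control and intervention households within one BMU.

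Difference-in-difference removes fixed differences between areas. Matching and propensity scores balance measured baseline characteristics. Neither removes an area's own change during the 12 months. That component is averaged only over the number of areas on each side, however many households are enrolled. A village-level term does not cure this either, because villages in the same area share the change.

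The number of areas per arm is therefore the figure that decides how strong the evidence can be, and the document's own figures do not yield a consistent one.

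**Working it through.** **1. The plan's own figure.** No SD or intracluster correlation is given, so 400 cannot be reproduced. With no design effect and 160 evaluable per side (200 × 0.8), 80% power for 0.20 requires SD = 0.20 × √(160/2) / (z_α + z_0.80). This is 0.64 two-sided or 0.72 one-sided.

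**2. Households against clusters.**
- Three arms: 3 × 4 × 50 to 75 = 600 to 900, not 400.
- Two groups: 2 × 4 × 50 = 400, which fits the original two-group plan.
- An arm of 100 at 50–75 per cluster holds 100/75 to 100/50 = 1.3 to 2 clusters. Four clusters in such an arm would have 25 households each.

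**3. Clusters against areas.**
- Cluster = village: 4/4 = 1 BMU per arm, so 3 BMUs for three arms or 2 for two groups.
- Cluster = BMU: 4 × 2 = 8 or 4 × 3 = 12 BMUs.
- Named areas: 5. If each is one BMU, neither reading gives five.
- Five whole areas over three arms split only as 1+1+3 or 1+2+2, so at least one arm is a single area. Pooling the intervention arms gives at best 2 v 3, with 5 − 2 = 3 df. On the village reading the pooled contrast is 2 v 1, with 1 df. One-sided 5% t critical values are 2.35 (3 df) and 6.31 (1 df).

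**4. False-positive rate of a household-level test.** Assumptions (none in the document): household SD of HAZ change 0.8, village SD 0.05, four villages per area, 160 v 160 evaluable, area SD of change s = 0.05, 0.10 or 0.15.

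V = s²(1/k₁ + 1/k₂) + 0.05²(1/v₁ + 1/v₂) + 0.8² × 2/160, where k counts areas and v villages on each side. The naive variance is V₀ = 0.64 × 2/160 = 0.008. Rejection rate = 1 − Φ(1.645 × √(V₀/V)).

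| Areas | V at s = 0.05 / 0.10 / 0.15 | Rejection under the null |
|---|---|---|
| 1 v 1 | 0.0143 / 0.0293 / 0.0543 | 11% / 19% / 26% |
| 2 v 1 | 0.0127 / 0.0239 / 0.0427 | 10% / 17% / 24% |
| 2 v 3 | 0.0106 / 0.0169 / 0.0273 | 8% / 13% / 19% |

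Simulation agrees, with about 8–18% at 2 v 3 and 11–26% at 1 v 1. With one BMU per arm (8 v 4 villages), a test on village means still rejects 5.9%, 11.1% and 16.5% of the time.

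**5. What a valid test costs.** At 2 v 3 areas, a t-test on area means (3 df) holds about 5%. For a true 0.20 its non-centrality is 0.20/√V = 1.94, 1.54 and 1.21. The non-central t gives 44%, 33% and 24% power. Simulation, which allows for unequal area sizes, gives about 23–41%. At 2 v 1 (1 df) the same formula gives about 22%, 17% and 13%.

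**6. Trap contrasts.** Table 1 words Hypotheses 7 and 8 as traps plus social marketing against control. If each of those arms is one area, between-area df = 1 + 1 − 2 = 0. The Analysis section's pooling rule exempts earnings (Hypothesis 8) but not yield (Hypothesis 7), which disagrees with Table 1. In a 1 v 1 contrast, a covariate constant within BMU (possibly coral cover or fishing ground area) cannot be distinguished from arm.

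**The case against.** Several points on the other side stand.

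- A reader might infer that every arm is one BMU. The document never says so. The inference rests on an ambiguous parenthesis that may only describe villages sampled within a BMU, and it gives three BMUs, which does not match five areas either. Treating an area as a BMU is itself an assumption.
- A reader might infer that no model could separate intervention from area for any hypothesis. For Hypotheses 1–5 that goes too far. Pooling leaves 2 v 1 or 2 v 3 areas, which is thin replication but not none.
- Nothing says the intervention group was split along BMU lines, so trap households could sit in more than one BMU. Nor does any section plan matched triplets of areas, so five not dividing by three is no defect.
- Home visits go to each household and cooking demonstrations to community spaces. The BMU-delivery argument is therefore weaker for the nutrition outcomes than for the fisheries ones. COVID livelihood effects are surveyed at both time points, so part of that shock could be adjusted for. Water temperature and seasonality vary over time and need not be aliased with arm.
- The study-design and study-area figures are not available here and may show the areas per arm. A missing cluster term alone could be left to an analysis plan.
- All variance inputs are assumed. At an area SD of 0.05, the village-level test is barely inflated.

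These points limit the claim but do not remove it. The cluster and household figures stated in the text disagree with one another, and the remedies offered for few clusters do not act on area-specific change.

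**Conclusion.** The concern holds in a limited form. The Sample size section's cluster count cannot be reconciled with five areas (if an area is a BMU), nor with three arms totalling 400 households.

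If areas are BMUs assigned whole, at least one arm is a single area. The primary nutrition contrast then has 3 df at best, or 1 df on the village reading. A household-level one-sided 5% test would reject falsely about 8–18% of the time at 2 v 3 areas. The 1 v 1 range of 11–26% would apply to the pooled contrast only if both intervention arms shared one BMU. Both ranges rest on the assumed SDs above, and only the direction is independent of them.

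Complete confounding with area is established only conditionally, for a contrast of two single-area arms. Traps v control as worded in Table 1 may be such a contrast, but the document does not settle it. This should be resolved before communities are assigned, because an unreplicated arm cannot be repaired in analysis.

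**What to change.** 1. In the Sample size section, name the allocation cluster (village, BMU or area). Restate villages, BMUs and areas for each of the three arms so that they agree with the five areas and with 200/100/100 households.
2. Analyse Hypotheses 1–5 with the allocation unit (area or BMU) as the top level and small-sample degrees of freedom, for example area-level change with df = areas − 2. Add leave-one-area-out results.
3. Restate the 80% power for that analysis, giving the SD and between-area variance used.
4. Where the trap arm or its comparator contains only one BMU, report Hypotheses 7 and 8 as area-by-area estimates without a P-value claim. Do not adjust that contrast for covariates constant within BMU. Reconcile the comparator for Hypothesis 7 between Table 1 and the Analysis section.

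The cost is wording and an analysis specification, with no extra households. The price in inference is real: wider intervals, stated power of perhaps 23–41% instead of 80% under the assumptions above, and a weaker claim for the trap hypotheses.

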### Setting

The study will be carried out in five distinct areas in Kilifi County, Kenya: Mayungu, Uyombo, Takaungu, Kuruwitu, and Kanamai (Figure 3). Study sites were chosen based on established relationships with the research team, receptivity to the proposed intervention, and proximity and access to marine resources. Kilifi County covers an area of 12,370 km^2^ with a population of 1.45 million and average household size of 4.8 persons (22, 23). The population primarily relies on small-scale fishing, farming activities (raising livestock, tree-cropping, and food-crop production), tourism, and migration to urban centers for their livelihoods (22). Close to half the population lives in poverty (46.4%) and the stunting prevalence (39%) is nearly double the national average, indicating high levels of malnutrition (20, 24). Education levels are low, and the populations are marginalized with limited formal rights to the marine resources on which many of their livelihoods depend.

